## Abstract

**Background:**

Only 5% of the molecules tested in oncology phase 1 trials reach the market after an average of 7.5 years of waiting and at a cost of tens of millions of dollars. To reduce the cost and shorten the time of discovery of new treatments, “drug repurposing” (research with molecules already approved for another indication) and the use of secondary data (not collected for the purpose of research) have been proposed. Due to advances in informatics in clinical care, secondary data can, in some cases, be of equal quality to primary data generated through prospective studies.

**Objective:**

The objective of this study is to identify drugs currently marketed for other indications that may have an effect on the prognosis of patients with cancer.

**Methods:**

We plan to monitor a cohort of patients with high-lethality cancers treated in the public health system of Catalonia between 2006 and 2012, retrospectively, for survival for 5 years after diagnosis or until death. A control cohort, comprising people without cancer, will also be retrospectively monitored for 5 years. The following study variables will be extracted from different population databases: type of cancer (patients with cancer cohort), date and cause of death, pharmacological treatment, sex, age, and place of residence. During the first stage of statistical analysis of the patients with cancer cohort, the drugs consumed by the long-term survivors (alive at 5 years) will be compared with those consumed by nonsurvivors. In the second stage, the survival associated with the consumption of each relevant drug will be analyzed. For the analyses, groups will be matched for potentially confounding variables, and multivariate analyses will be performed to adjust for residual confounding variables if necessary. The control cohort will be used to verify whether the associations found are exclusive to patients with cancer or whether they also occur in patients without cancer.

**Results:**

We anticipate discovering multiple significant associations between commonly used drugs and the survival outcomes of patients with cancer. We expect to publish the initial results in the first half of 2024.

**Conclusions:**

This retrospective study may identify several commonly used drugs as candidates for repurposing in the treatment of various cancers. All analyses are considered exploratory; therefore, the results will have to be confirmed in subsequent clinical trials. However, the results of this study may accelerate drug discovery in oncology.

**International Registered Report Identifier (IRRID):**

DERR1-10.2196/48925

## Introduction

The usefulness of new cancer treatments is traditionally analyzed in clinical trials, which are considered the most rigorous design to study the effects of a treatment on a disease. Despite their strengths, clinical trials have significant limitations, such as cost and time. In a typical clinical trial, one or very few treatments are tested over a course of 7.5 years, and in oncology, the costs range from US $4.5 million (phase I) to US $22.1 million (phase III) [1-4]. Despite this, the clinical trials database ClinicalTrials.gov registers more than 22,000 trials each year, accounting for billions spent annually on clinical trials [5].

In oncology, the results of this substantial financial investment are modest, at best. As an example, only 5% of the molecules tested in phase 1 trials are marketed, and even if they are, they rarely generate a substantial change in the prognosis of patients [6,7]. In addition, the issue seems to be getting worse because the number of approved molecules has not increased in recent decades, but investment by the pharmaceutical industry has increased significantly [8].

Various strategies have been used to try to improve the efficiency of clinical trials. One of the most interesting is drug reuse (drug repurposing), with the aim of finding new uses for existing drugs approved for another therapeutic indication. This approach can, in most cases, allow research to begin with phase 2 trials because preclinical, pharmacokinetic, pharmacodynamic, and toxicity data are usually already known [7]. Looking for new treatments among already known molecules does not seem unreasonable, because in Spain alone, there are more than 2600 active ingredients approved and in use; it makes sense to think that some of them may have unknown effects on cancer. This approach, however, faces significant challenges since the complex and heterogeneous nature of cancer means that drugs with an effect on one type of cancer may not exhibit similar efficacy in several subtypes of cancer. Additionally, issues related to intellectual property, regulatory pathways, and the need for robust clinical evidence contribute to the complexity of drug repurposing efforts in oncology [9,10].

Another approach that substantially lowers the cost of pharmacological discoveries is the use of secondary data for research. Secondary data, which are used in some epidemiological designs, are those that are not collected for the purpose of the investigation but for another purpose, generally before the start of the study. Traditionally, data of this type are of poor quality because they are collected for other purposes, without the rigor of prospective studies. The number of variables may be incomplete because the data collection was not designed to address the research question. However, the technological revolution in recent decades has led to a paradigm shift, leading to reconsiderations of the classic axiom that secondary data are of low quality. New technologies and social networks produce a substantial amount of population data, which are not always of poor quality. The application of these technologies to medicine has led to the implementation of electronic health records and electronic prescription. Although the data in these 2 registries are not research data, they are of high quality, as they are used in clinical practice to manage people’s health. Electronic prescription in Catalonia, for example, is how treatments are prescribed to users of the National Health System; therefore, it contains the drugs, doses, and guidelines actually prescribed to millions of people by their doctors. In addition, these doctors do not type the active ingredients in the prescription, which could lead to errors, but rather select them from lists in drop-down windows; therefore, the database is completely encrypted and does not contain transcription errors, in addition to being continuously updated. Other current databases, such as the mortality registry of the National Institute of Statistics (INE) or the Minimum Basic Data Set (CMBD) registry, where the diagnoses and procedures performed on hospitalized patients in Spain are recorded, can offer sufficient quality, in combination with electronic prescription, to draw conclusions about some of the effects of commercialized drugs [11,12].

Thus, combining the 2 strategies discussed above, we have designed a drug epidemiological study using population databases to identify drugs whose consumption is associated with changes in the survival of patients with cancer. For this, the pharmacological agents consumed by long-term survivors of incurable cancer will be compared with the drugs consumed by patients with shorter survival. We hope that this will allow, with a minimum investment of time and money, the identification of hitherto unknown effects of the molecules marketed in Spain on various oncological diseases.

This paper presents the general protocol for the study; the primary objective is to identify drugs whose consumption influences the survival of patients with high-lethality cancer (defined as those with a 5-year average survival of less than 20%, according to the statistics available at the time of database creation), and the secondary objective is to study the relationship between nonneoplastic diseases of patients with cancer and their survival. Given the diversity of the expected results with respect to different drugs and cancer diseases, we plan to publish the most relevant results in independent papers, in which the methodological details of each substudy will be described, as well as the specific interpretation of the results and their implications, depending on the nature of the findings and the associated cancer.

## Methods

### Design

This will be a retrospective cohort study in which a cohort of patients with high-lethality cancer (cohort 1) and another control cohort composed of people without cancer (cohort 2) will be studied.

### Participants and Settings

The study population will be patients with the following cancers whose estimated survival at 5 years is less than 20%: lung, pancreas, esophagus, gastric carcinomas, hepatocarcinoma, and metastatic cancers.

Cohort 1 will include all patients registered in the databases of the public health system in Catalonia (Spain) who were diagnosed with any of the diseases under study between 2006 and 2012 (Textbox 1 contains the list of International Classification of Diseases, Tenth Revision [ICD-10] codes) and who have complete data regarding the study variables (see “Outcome Measurements and Variables” section).

Diagnostic codes (International Classification of Diseases, Tenth Revision [ICD-10]) for the pathologies under study.
**Neoplasm lung**
C34.0, C34.00, C34.01, C34.02, C34.1, C34.10, C34.11, C34.12, C34.2, C34.3, C34.30, C34.31, C34.32, C34.8, C34.80, C34.81, C34.82, C 34.9, C34.90, C34.91, and C34.92
**Neoplasm pancreas**
C25, C25.0, C25.1, C25.2, C25.3, C25.7, and C25.9
**Neoplasm hepatic**
C22, C22.0, C22.1, C22.2, C22.3, C22.4, C22.7, C22.8, and C22.9
**Neoplasm gastric**
C16, C16.0, C16.4, C16.3, C16.1, C16.2, C16.5, C16.6, C16.8, and C16.9
**Neoplasm esophagus**
C15, C15.3, C15.4, C15.5, C15.8, and C15.9
**Metastasis**
C78.0, C78.00, C78.01, C78.02, C78.1, C78.2, C78.3, C78.30, C78.39, C78.4, C78.5, C78.6, C78.7, C78.8, C78.80, C78.89, C79.0, C79.00, C79.01, C79.02, C79.1, C79.10, C79.11, C79.19, C79.2, C79.3, C79.31, C79.32, C79.4, C79.40, C79.49, C79.5, C79.51, C79.52, C79.6, C79.60, C79.61, C79.62, C79.7, C79.70, C79.71, C79.72, C79.8, C79.81, C79.82, C79.89, C79.9, and C80.0

In cohort 2, a total of 4 control participants will be included for each patient with cancer included in cohort 1. Control participants will be selected from those registered in the databases of the public health system in Catalonia whose diagnostic codes do not include neoplasm diseases (ICD-10 codes C00 to D49). The 4 control participants will be matched with the cases in cohort 1 by place of residence and date of birth, of which 2 controls will have been born in the same year and the other 2 controls will have been born 10 years earlier, with the aim of generating an older subcohort with, therefore, higher expected mortality.

Participants who, due to their unique health characteristics, including rare diseases or peculiar sociodemographic data such as extreme ages or residing in sparsely populated areas, were at risk of being identified were excluded from the sample.

### Duration

The patients in cohort 1 will have been diagnosed with the cancer under study between 2006 and 2012, both inclusive, and their survival will be retrospectively monitored for 5 years after diagnosis or until death if it occurs earlier. Cohort 2 will include patients without cancer who have had any type of contact with the health care system between 2006 and 2012, and these individuals will be followed up retrospectively for 5 years or until death if it occurs earlier.

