Hospital CMBD is a database in which diagnoses and procedures performed on hospitalized patients are recorded throughout the Spanish territory; all public hospitals and the majority of private hospitals (>95% hospital coverage) are included [14].Estació Clínica d'Atenció Primària (ECAP) is an electronic medical history program launched in 2001 and used by family doctors, pediatricians, and nurses from the Catalan Institute of Health (Institut Català de la Salut [ICS]) primary care centers when they visit patients; it includes all previous illnesses known to the primary care physician and records of the health care process in the outpatient setting, including assessments by health care personnel, diagnostic tests, and treatment, among others. The PADRIS program has only provided data since 2006, after which data are considered to be of good quality.The registry of causes of death is prepared by the INE using data from the Medical Certificate of Death or Statistical Bulletin of Death, Statistical Bulletin of Judicial Death, and Statistical Bulletin of Childbirth. It is prepared following the criteria established by the WHO (World Health Organization) in the International Classification of Diseases (ICD), which includes more than 12,000 diseases.Electronic prescription has been implemented in Catalonia progressively since 2010 and is currently deployed in 100% of primary care centers, pharmacies, and public hospitals in Catalonia. Prescribing and dispensing data will be obtained from the Comprehensive Health Information System of the Catalan Health Service (Servei Català de la Salut [CatSalut]), which is a computerized system used by the doctors of the national health system in Catalonia to prescribe financed pharmacological treatments to their patients and the pharmacies to dispense them; it contains information on the date of the prescription, the active ingredient, and dose, among other variables. Unfunded treatments can be prescribed using this tool but are often prescribed by other means (paper prescriptions).

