### Outcome Variables and Measurements

The primary end point is survival, calculated from the date of entry in the database until death or until 5 years of follow-up are reached. For patients in cohort 1, the earliest date of cancer diagnosis for which they have been selected to be part of the cohort will be considered the date of entry into the study (inclusion criterion).

As study variables, the following data will be collected from all patients:

List of diagnosed diseases (data source: CMBD and ICS ECAP diagnostic registry)Date of death (data source: INE cause of death registry)Cause of death (data source: INE cause of death registry)Pharmacological treatment (data source: Catalan electronic prescription), including all prescribed active ingredients, drug withdrawal dates from pharmacies, consumed doses, and prescribed regimen, during the entire follow-up periodSex (data source: Sistema Integral d'Informació de Salut)Date of birth (data source: Sistema Integral d'Informació de Salut)Basic health area (data source: Sistema Integral d'Informació de Salut)

For the patients included in the study with one of the cancers under study (cohort 1), the following variables will also be collected:

Type of cancer and presence of metastases (data source: CMBD and ICS ECAP diagnostic registry)Date of diagnosis for which the patient is included in the cohort (data source: CMBD and ICS ECAP diagnosis registry)Surgical treatment of the cancer (data source: CMBD)Date of surgical treatment (data source: CMBD)

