As a secondary objective, we plan to analyze the relationship between the presence of various nonneoplastic diseases and the survival of patients with cancer. To do this, we will compare the survival of patients with a specific disease to those who do not have it, adjusting multivariate models for age, gender, other conditions that may impact survival, and medications that have previously been shown to modify survival in previous analyses.

All analyses conducted in the cohort of patients with cancer will be replicated in a control patient group matched by age to the patients with cancer (with expected lower mortality) and in another group of older patients, where each control will be 10 years older than their cancer counterpart (with expected higher mortality). The findings that are reproduced in these groups of the control cohort will be discarded, as they are considered the result of uncontrolled biases or general effects on survival, not related to the cancers under study.

To consider a result statistically significant, the P value will be set at P=.05. All analyses are considered exploratory and hence subject to confirmation in new studies; therefore, no correction techniques will be applied to the P values obtained. All statistical analyses will be performed using R statistical software (version 4.1.0 or higher; R Core Team).

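### The control cohort's time zero is undefined and not tied to the matched patient's diagnosis date, so age at entry, calendar period and exposure window are not aligned within matched sets

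*Protocol article*

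**What the plan says.** The Outcome Variables and Measurements section sets one origin for everyone: "The primary end point is survival, calculated from the date of entry in the database until death or until 5 years of follow-up are reached". It then gives that origin a concrete meaning for cancer patients only: "For patients in cohort 1, the earliest date of cancer diagnosis for which they have been selected to be part of the cohort" counts as entry.

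For controls, the Duration section says: "Cohort 2 will include patients without cancer who have had any type of contact with the health care system between 2006 and 2012". Observation then lasts 5 years, or less if the person dies sooner. The section gives no start date for those 5 years.

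The Participants and Settings section, in the paragraph on cohort 2, says that the four controls per patient are "matched with the cases in cohort 1 by place of residence and date of birth": two born in the same year and two born 10 years earlier. No calendar date is part of the match.

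The Statistical Analysis section repeats every cancer-cohort analysis in both control groups. It describes the first as matched by age, and says of the second that "each control will be 10 years older than their cancer counterpart". Findings that reproduce in controls are discarded. The section on potential sources of bias handles immortal time with landmark windows counted from cancer diagnosis; its example is month 3.

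**The concern.** A birth-year match fixes the age difference on any shared calendar date. It fixes the age difference at the start of follow-up only if the patient and the control start on the same date, and the article does not require this.

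The control cohort serves as a filter: an association that also appears in people without cancer is dropped as bias or as a general survival effect. The filter works only if the control analysis has the same structure as the patient analysis. If controls start in a different year, at a different age and with a different exposure window, a general effect or an artefact may fail to reproduce for those reasons and then be kept as cancer specific. The Statistical Analysis section applies no correction to P values (the Discussion leaves a false discovery rate adjustment open), which adds to the weight on this step.

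The landmark method raises a further problem. Its windows start at cancer diagnosis, a date that controls do not have. Without an assigned index date, the promised replication has no defined origin.

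**Working it through.** The plan gives no figure for this point. Its sample-size figure (294 per group for 20% versus 30%, two-sided 5%, 80% power) reproduces with the pooled-variance formula and is not affected.

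**Inputs from the article.** The accrual window is 2006-2012, or 7 years. Controls are born in the same year or 10 years earlier. Electronic prescription starts in 2010, progressively.

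**Assumptions, not in the article.** Diagnosis dates are uniform over the 7 years, so the mean is 3.5 years after the start of 2006. Two readings of control entry are tried, because the article states neither.

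**Bound.** Both dates lie in a 7-year window, so they can differ by up to about 7 years. Near that extreme, a patient born in 1940 and diagnosed in 2012 is 72. A control born in 1940 and entering in 2006 is 66. One born in 1930 is 76, which is 4 years older than the patient and not 10.

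**Reading A: entry at first contact.** With r contacts a year and at least one in the window, mean entry = 1/r − 7e^(−7r)/(1 − e^(−7r)). The mean gap is 3.5 minus this. The share entering before 2010 is (1 − e^(−4r))/(1 − e^(−7r)).

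| r per year | mean entry (years after the start of 2006) | mean gap before diagnosis (years) | mean age excess of the 10-years-older group (years) | entering before 2010 |
|---|---|---|---|---|
| 0.1 | 3.1 | 0.4 | 9.6 | 65% |
| 1 | 1.0 | 2.5 | 7.5 | 98% |
| 5 | 0.2 | 3.3 | 6.7 | about 100% |

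The same-birth-year controls would be younger than their patients at entry by the mean gap shown.

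**Reading B: entry at a random date in the window.** The mean gap is 0, the mean absolute gap is 7/3 = 2.3 years, and (6/7)² = 73% of pairs differ by more than 1 year. The share entering before 2010 is 4/7 = 57%.

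**With the matched diagnosis date as index.** The gap is 0 and the age difference at entry is 0 or 10 years, within the birth year. The share of controls entering before 2010 is 4/7 = 57%, the same as for patients.

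Simulation of both readings gave the same values.

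**The case against.** The strongest reply is that the article does not specify a wrong time zero; it leaves one unspecified. It is a condensed general protocol that defers details to substudy papers. Controls are matched individually and all analyses are to be repeated in them, which is compatible with using the patient's date. This stands in part. However, the article does state an origin for both cohorts, defines it for one and lists the matching variables, and as written these do not align the two cohorts.

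Four stronger readings are tempting but not supported:

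- **Controls start at their first contact.** Contact is an eligibility condition, and the word first does not appear. Reading A is only one possibility.
- **The age match fails.** Birth-year matching stands. Only age at entry can drift.
- **Hardly any controls have early drug exposure on record.** It is true that "Electronic prescription has been implemented in Catalonia progressively since 2010", and under Reading A most controls would enter before then. But that rests on assumed contact rates. About 57% of patients also enter before 2010 under uniform diagnoses, and every full 5-year follow-up reaches at least the start of 2011. Patients without prescription records are rejected, and the article does not say whether dispensing data reach further back. This is a separate, study-wide matter.
- **The controls are the only guard against bias.** The plan also has matching, adjustment and three named bias measures.

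Nor does lower mortality in younger-entering controls by itself bias a comparison of exposed with unexposed controls. The plan deliberately uses control groups with lower and higher expected mortality. The harm lies in unaligned windows and periods, not in the mortality level.

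**Conclusion.** The point holds in this form: the control index date is undefined and not tied to the matched patient's diagnosis, so age at entry, calendar period and exposure window are not secured within matched sets. The mismatch can reach about 7 years. Under uniform diagnosis dates, controls enter on average 0.4 to 3.3 years early if entry is the first contact at 0.1 to 5 contacts a year; for a random entry date the mean absolute gap is 2.3 years. The contact rates and the uniform dates are assumptions, and the article does not say which reading applies. That nothing in the text aligns the dates needs no assumption.

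The direction of concern is a missed replication in controls, which lets a general effect or an artefact pass as cancer specific. How often this would happen cannot be calculated from the article. All results are declared exploratory, which limits the consequence but does not repair the filter. The Results section says that analyses have begun, so the date should be settled before any finding is kept or discarded on the strength of the controls.

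**What to change.** In the Duration and the Outcome Variables and Measurements sections, give each control the diagnosis date of its matched patient as index date. Require the control to be alive and registered on that date. Count the 5-year follow-up, the landmark windows and drug exposure in controls from it, and say in the bias section that the landmarks run from this index date in both cohorts.

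The cost is a few sentences and re-indexing of data already held. The downside is the loss of some controls who died before the index date or were not registered on it. The change makes the share entering before 2010 the same in matched patients and controls, but it does not remove the early prescription gap, which needs its own answer for both cohorts.
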